#### Secondary Outcomes

The secondary outcomes measures are quality of life, self-efficacy, patient satisfaction, and Web-based analytics. These will be assessed using the tools listed below.

The EuroQol EQ-5D-5L assessment will be utilized in this study. It is a 5-level 5-dimension standardized assessment tool, used to measure health-related quality of life. The 5 dimensions include: mobility, self-care, usual activities, pain or discomfort, and anxiety or depression. The tool includes a visual analogue scale where participants are asked to rate their health on a scale from 0 to 100, where 0 means the worse health you can imagine and 100 means the best health you can imagine [16].

The Self-Efficacy for Managing Chronic Disease (SEMCD), is a validated tool consisting of six items on a 10-point scale measuring a participant’s level of confidence in doing certain activities, 1 being “not at all confident” and 10 being “totally confident” [17].

Patient satisfaction with the program will be explored using a patient satisfaction survey developed by the research team. The developed survey comprises of 6 closed questions and 2 open questions for participants in both arms of the trial. Participants in the eHealth program will receive additional survey questions on the usability of the app, consisting of 13 closed questions and 3 opened-ended questions.

For participants in the eHealth program additional data on their utilization of the eHealth educational program will be collected through Web-based analytics. This will include information on the modules accessed, length of time spent on each module, and satisfaction ratings prompted within the program.

### Economic Evaluation

A cost-effectiveness analysis comparing the developed eHealth program to standard care will be conducted from the hospital’s perspective on an intention-to-treat basis. Direct costs will include the service delivery costs associated with each program (brochures, photocopying, and Web-based application fees) as well as the cost of follow-up care (the time spent by health professionals organizing and providing face-to-face sessions, replying to emails, making telephone calls, and managing and monitoring online content). Cost data will be collected from pre-admission through to 6 months postdischarge using hospital medical records. Outcomes will include changes in HOOS and quality of life (measured using the EQ-5D-5L). Incremental cost-effectiveness ratios (comparing the difference in cost between the eHealth program and standard care with the difference in the outcomes) will be calculated for HOOS and Quality Adjusted Life Years, and sensitivity analysis will be conducted on the key parameters.

### Sample Size

Sample size calculations were conducted based on the primary outcome, the HOOS. Existing data were used to determine the minimal clinically important improvement [18] and SD [19]. Based on a power of 90% and 5% significance level, 42 patients per group are needed. To allow for a dropout rate of approximately 15%, a sample size of 50 per group is required. Therefore, the estimated required sample size for the study is 100 participants.

### Statistical Analysis

Data will be reported in accordance with the Consolidated Standards of Reporting Trial (CONSORT). Mean (SD), median (interquartile range) and percentages will be used to describe the characteristics of the study group.

An analysis of covariance will be used to assess the primary outcome. The covariables will include age, gender, type of surgery, length of stay, RAPT score, and other comorbidities. Treatment effects will be calculated on the pre-to-post intervention outcomes at 6 weeks. Further analysis will be performed on the posttreatment effects at 3 months and 6 months postsurgery. The clinical treatment effect of each intervention group will be further analyzed using independent *t* tests, tests of medians, nonparametric tests, and chi-squared tests on pre-to-post intervention changes across the range of outcome measures and patient satisfaction.

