### Outcome Assessment

Outcome measures will be collected at four time points, namely at pre-admission, 6 weeks, 3 months and 6 months after the surgery. Figure 2 presents a flow chart of the recruitment and trial participation process and Table 1 outlines the outcome assessments used in this study, as well as the collection time points for the assessments. Participants will be asked to complete the relevant assessments online and an email reminder will be sent to each participant when the assessment is due, followed by a reminder one week later.

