#### Primary Outcome

The primary outcome is patient-reported evaluation of symptoms and function limitations related to the affected hip (the hip undergoing surgery). The measure of this outcome is the Hip Dysfunction and Osteoarthritis Outcome Score (HOOS) version LK 2.0. The HOOS is a validated 40-item questionnaire where patients self-assess their hip across 5 subscales: (1) symptoms and stiffness, (2) pain, (3) function of daily living, (4) sports and recreational activities function, and (5) quality of life [15].

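### Pre-admission HOOS is collected but not named among the ANCOVA covariables, and the further tests on changes are unadjusted, so available precision and protection against chance baseline imbalance are not secured

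*Protocol article*

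**What the plan says.** All of this is in the protocol article.

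- **Model (Statistical Analysis).** "An analysis of covariance will be used to assess the primary outcome".
- **Covariates (same section).** "The covariables will include age, gender, type of surgery, length of stay, RAPT score, and other comorbidities". That is six entries. Pre-admission HOOS is not one of them, and no other section puts it into a model.
- **Response and time point (same section).** "Treatment effects will be calculated on the pre-to-post intervention outcomes at 6 weeks". Analyses at 3 and 6 months follow.
- **Further tests (same section).** After independent t tests the list continues with "tests of medians, nonparametric tests, and chi-squared tests on pre-to-post intervention changes across the range of outcome measures". No adjustment is mentioned for any of these.
- **Data available (Outcome Assessment and Table 1).** Measurements are taken "namely at pre-admission, 6 weeks, 3 months and 6 months after the surgery". Table 1 ticks HOOS, EQ-5D-5L and SEMCD at pre-admission. Satisfaction is ticked at 6 weeks only, and web analytics apply to the eHealth arm only.

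**The concern.** For a patient-reported score measured before and after surgery, the score's own baseline is usually the most useful covariate. The article is not silent on covariates: it gives a list, and the outcome's baseline is not on it. The sentence on treatment effects leaves the response open, and without a baseline term neither possible response is a good choice:

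- The **6-week score alone** ignores the baseline, so part of any chance baseline difference carries through to the estimate.
- The **change score** subtracts the whole baseline, which over-corrects whenever the regression of follow-up on baseline has a slope below 1.

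At stake are precision that the trial has already collected the data for, and how far the reported effect depends on which arm happened to start with better hips. The Randomization section describes blocking only and no stratification by baseline HOOS, so nothing in the stated design limits such a difference.

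**Working it through.** **Inputs.** From the Sample Size section: 42 evaluable per group, 90% power, 5% significance (two-sided assumed), about 15% dropout, 50 per group. Not given in the article: the target difference, the SD, whether that SD is for a single time point or for change, and the correlation r between pre-admission and 6-week HOOS. I therefore take r from 0.2 to 0.8 as an assumed range.

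**Reproducing the plan's figure.** 42 / 0.85 = 49.4, rounded up to 50 per group, 100 in total. This agrees. The 42 cannot be rebuilt without the difference and SD. Inverting the usual formula gives the standardized difference it implies: √2 × (1.960 + 1.282) / √42 = 0.707 (0.716 with the t distribution).

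**Relative variance of the treatment effect.** Take the 6-week score variance as 1, equal SDs at both times and no other covariates:

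- 6-week score, no baseline term: 1
- change score, no baseline term: 2(1 − r)
- ANCOVA with baseline: 1 − r²
- ratio of change to ANCOVA: 2(1 − r) / (1 − r²) = 2 / (1 + r)
- ratio of 6-week score alone to ANCOVA: 1 / (1 − r²)

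| r | change 2(1 − r) | ANCOVA 1 − r² | change / ANCOVA | 6-week alone / ANCOVA |
|---|---|---|---|---|
| 0.2 | 1.60 | 0.96 | 1.67 | 1.04 |
| 0.3 | 1.40 | 0.91 | 1.54 | 1.10 |
| 0.5 | 1.00 | 0.75 | 1.33 | 1.33 |
| 0.6 | 0.80 | 0.64 | 1.25 | 1.56 |
| 0.8 | 0.40 | 0.36 | 1.11 | 2.78 |

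In standard errors, the change score is √1.67 = 1.29 times as wide at r = 0.2 and √1.25 = 1.12 times at r = 0.6. Below r = 0.5 the change score is the noisier of the two unadjusted forms; above it, the 6-week score is.

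**Does the direction need equal SDs?** No. If the baseline SD is k times the 6-week SD, the change variance is 1 + k² − 2kr. Its excess over ANCOVA is 1 + k² − 2kr − (1 − r²) = (k − r)², which is never negative. Only the size moves: at k = 0.8 and r = 0.3, 1.16 / 0.91 = 1.27 instead of 1.54.

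**Chance imbalance.** With 42 per group the baseline mean difference has standard error √(2/42) = 0.218 SD, so a difference beyond 0.2 SD in either direction has about a 36% chance. Given a difference of +0.2 SD, and equal SDs:

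- change score shifts by (r − 1) × 0.2: −0.14 SD at r = 0.3, −0.10 SD at r = 0.5
- 6-week score shifts by r × 0.2: +0.06 SD at r = 0.3, +0.10 SD at r = 0.5
- ANCOVA with baseline removes the shift, given a linear relation.

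**Power, conditionally.** If the planning SD is a single-time-point SD, the SDs are equal and there are no other covariates, then 42 per group with d = 0.707 gives, for change against baseline-adjusted ANCOVA: 78% and 92.5% at r = 0.3; 90% and 96% at r = 0.5; 95% and 98% at r = 0.6. If the planning SD was already that of the change, the variance ratios stand but these power figures do not.

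**The case against.** **The baseline may already be intended.** The covariate sentence is not worded as exhaustive, and the sentence on treatment effects speaks of outcomes; the word changes appears only for the further tests. An ANCOVA of pre-to-post outcomes could be meant to carry the pre-score, and a separate analysis plan may say so. This stands as a limit: the article does not establish that the primary analysis is an unadjusted change score, and a reader should not infer that. It does not remove the point, because the published list omits the covariate and the further tests on changes are unadjusted on any reading.

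**The trial may seem underpowered.** A reader might infer this from the 78% at r = 0.3. The documents do not support it. The value of r and the basis of the SD are unknown, and the planned model has other covariates. RAPT, for instance, includes walking distance and gait-aid use, which are plausible proxies for baseline function. If the covariates explained 10% to 20% of the change variance (assumption), the 78% would become 82% to 87%. With a baseline SD of 0.8 times the follow-up SD it would be 85%. At r of 0.5 or more the 90% is kept even on change scores, under the stated assumptions.

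**Randomization removes bias.** Correct over repeated trials. The imbalance argument concerns this trial's realised baseline difference only.

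**The further tests are not rivals to the ANCOVA.** Largely fair. They are introduced as further analysis and can be read as chosen by data type, not as several tests on every outcome. Competing p-values are therefore a secondary matter of labelling.

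**Conclusion.** The point holds as one of efficiency and robustness. The article lists covariables for the HOOS ANCOVA without the pre-admission score that it collects, leaves open whether the response is the 6-week score or the change, and prescribes further tests on changes without adjustment. For r between 0 and 1, either response without a baseline term is less precise than the baseline-adjusted ANCOVA. For change scores the variance ratio is 1.67 to 1.25 over r = 0.2 to 0.6, assuming equal SDs and no other covariates. The direction for change scores does not depend on equal SDs; the size depends on r, the SD ratio and what the listed covariates recover.

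It is not shown that the sample size is wrong, that the 90% power is missed, or that the estimate is biased over randomization. Nor does the point reach every outcome. Satisfaction is measured once and web analytics exist in one arm, so neither has a baseline score to adjust for. HOOS, EQ-5D-5L and SEMCD are the outcomes concerned.

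**What to change.** - State that the primary analysis is an ANCOVA of the 6-week HOOS score, and add the pre-admission score of the same HOOS scale to the covariates.
- Use the same baseline-adjusted model for HOOS at 3 and 6 months, and for EQ-5D-5L and SEMCD with their own pre-admission scores.
- Label any unadjusted t, median or rank tests on changes in these outcomes as sensitivity analyses. Leave the chi-squared tests for categorical satisfaction items as they are.

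The cost is one degree of freedom per model and a few lines of wording. No new data are needed. If the baseline score was always meant to be in the model, saying so settles that part of the point.

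### HOOS is described as analysed one visit at a time; a joint model of the three follow-ups would cheaply protect the 3- and 6-month effects against loss that differs by arm

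*Protocol article*

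**What the plan says.** All references are to the protocol article.

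- **Outcome Assessment:** "Outcome measures will be collected at four time points, namely at pre-admission, 6 weeks, 3 months and 6 months after the surgery". Questionnaires are completed online, with an email when one is due and a reminder a week later.
- **Statistical Analysis:** "An analysis of covariance will be used to assess the primary outcome". On timing: "Treatment effects will be calculated on the pre-to-post intervention outcomes at 6 weeks". Then: "Further analysis will be performed on the posttreatment effects at 3 months and 6 months postsurgery". The model for the two later visits is not named.
- **Covariates:** "The covariables will include age, gender, type of surgery, length of stay, RAPT score, and other comorbidities". No HOOS score is listed, from baseline or any other visit.
- **Sample Size:** "Based on a power of 90% and 5% significance level, 42 patients per group are needed", and "To allow for a dropout rate of approximately 15%, a sample size of 50 per group is required".

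The article gives no rule for missing HOOS scores. It mentions intention-to-treat only for the economic evaluation.

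**The concern.** Three correlated follow-up scores per patient are collected, but the analysis is set out visit by visit. In an ordinary ANCOVA of the 6-month score, a patient who answered at 6 weeks and 3 months but not at 6 months contributes nothing. The earlier scores, which may help to explain why the patient stopped answering, go unused.

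This matters if the reasons for stopping differ by arm, and the design makes that plausible. Participants know their allocation and the outcome is self-reported on an online form. Only the intervention arm is encouraged to log in daily, receives the program's automatic emails and can reach the care team through the program. The intervention could therefore change who answers an online questionnaire. Raising the sample size to allow for dropout restores precision but does not remove selection.

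At stake are mainly the 3- and 6-month contrasts, and to a lesser extent the 6-week one.

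**Working it through.** **1. The plan's own figure.** 42 / (1 − 0.15) = 49.4, rounded up to 50 per group, 100 in total. The dropout allowance is correct. With exactly 15% lost, 50 × 0.85 = 42.5 per arm remain.

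**2. Implied target effect.** The article prints neither the difference nor the SD. Solving backwards from 42 per group, 90% power and 5% significance (two-sided assumed): δ/SD = (1.960 + 1.282) × √(2/42) = 0.707.

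**3. Power, visit by visit versus joint.** Power = Φ(0.707/√v − 1.96), in SD units. For a single-visit analysis v = 2/n. For the joint model v comes from the three-visit information matrix, with equal correlation between visits of 0.3-0.7 (assumed) and 50 randomised per arm.

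| Pattern of loss (assumed) | Visit | Visit by visit | Joint |
|---|---|---|---|
| All 15% lost before 6 weeks | any | 90.3% | 90.3% |
| Monotone 5/10/15% | 6 weeks | 93.2% | 93.2% |
| Monotone 5/10/15% | 3 months | 91.9% | 92.0-92.5% |
| Monotone 5/10/15% | 6 months | 90.3% | 90.7-91.9% |
| Random gaps, 15% at each visit | any | 90.3% | 90.8-92.5% |

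In the last row the single-visit variance is about 2% larger than the joint variance at correlation 0.3 and about 9% larger at 0.7. The planned power survives a visit-by-visit analysis, and the joint model adds at most about 2 points.

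**4. Bias at a later visit when loss depends on the 6-week score.** As an upper bound, suppose the lowest 15% at 6 weeks in one arm all drop out and loss in the other arm is random. The mean 6-week score of those remaining shifts by φ(1.036)/0.85 = 0.233/0.85 = 0.274 SD. The later visit shifts by the correlation times that amount:

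- selection in one arm: 0.3 × 0.274 = 0.08 SD to 0.7 × 0.274 = 0.19 SD;
- opposite selection in the two arms: twice that, 0.16 to 0.38 SD;
- same mechanism in both arms: the shifts cancel, giving about 0.

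Simulation with the same three mechanisms gave 0.09-0.19, 0.16-0.38 and about 0 SD.

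A sharp cut-off is the strongest form this dependence can take. At correlations 0.55-0.65 it gives 0.15-0.18 SD (one arm) and 0.30-0.36 SD (opposite). A further simulation at those correlations, with SD 18, gave about half as much at 3 and 6 months:

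| Selection | Per-visit ANCOVA bias | In SD | Share of 0.707 |
|---|---|---|---|
| One arm | 1.3-1.6 points | 0.07-0.09 | 10-13% |
| Opposite | 2.6-3.2 points | 0.14-0.18 | 20-25% |

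The joint model was off by 0.15 points or less.

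**5. The 6-week effect.** Under monotone dropout a patient missing at 6 weeks has no later score, so a joint model has nothing to add. It can help only if patients skip 6 weeks and return. Simulated with opposite selection by arm:

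- gap depends on the 3-month score: bias −3.0 points by visit, +0.2 joint;
- gap depends on the unseen 6-week score: −5.2 by visit, −3.3 joint, so 3.3/5.2, about two thirds, remains.

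**The case against.** **The article does not commit to discarding data.** A reader might infer that HOOS will be analysed by separate complete-case ANCOVAs. The article says neither. The later model is unnamed, missing-data handling is commonly left to a fuller document that is not shown, and ANCOVA after multiple imputation using the other visits would fit the text and recover much the same information. This objection stands, and it is why the point is not an error in the plan. What remains is that the article names a model and sets it out by visit.

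**Bias does not follow from missingness alone.** A reader might infer that a single-visit ANCOVA is biased whenever missingness depends on other visits. For the arm difference that is false: if loss works the same way in both arms, the bias is about zero. Nothing in the documents shows that it will differ by arm, and opposite selection is an extreme case. This limits the claim to a risk.

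**The 6-week result is largely untouched.** A reader might infer that the main effect is compromised. The sample-size section speaks of dropout, and under monotone dropout both analyses give the same 6-week answer. If the gap depends on how the patient feels at 6 weeks, the joint model removes only part of the bias.

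**Precision is already covered.** The allowance from 42 to 50 holds power at about 90%. This also stands, so the case rests on bias at 3 and 6 months.

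**Conclusion.** The point holds as a moderate, inexpensive recommendation. As described, the visit-by-visit ANCOVA leaves usable HOOS scores out of the 3- and 6-month comparisons. If loss after 6 weeks depends on the 6-week score differently by arm, those effects could be off by about 0.07-0.09 SD (selection in one arm) or 0.14-0.18 SD (opposite selection). That is roughly a tenth to a quarter of the implied 0.707 SD target.

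These sizes rest on an assumed SD of 18, visit correlations of 0.55-0.65 and about 15% loss related to the 6-week score; the article gives only the 15%. Sharper selection would give more, and a common mechanism gives about nothing. The gain in precision is minor, and the 6-week contrast gains only from patients who miss that visit and return.

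**What to change.** Analyse HOOS at 6 weeks, 3 months and 6 months in one linear mixed model for repeated measures:

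- fixed effects for arm, visit, arm-by-visit, baseline HOOS, baseline-by-visit and the pre-randomisation covariates (length of stay, which arises after randomisation, is not one of these);
- unstructured covariance across visits;
- every randomised patient with at least one follow-up score, in the arm allocated.

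Keep the 6-week arm contrast primary and take the 3- and 6-month contrasts from the same fit.

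The cost is revised wording and slightly more modelling work, with no new data, visits or patients. The model relies on data being missing at random given the observed scores, so it will not remove bias from gaps that depend on the unseen score itself. If a fuller document already specifies imputation using the other visits, saying so would largely meet the point.

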## Results

Enrollment in the study commenced in January 2018 with recruitment due for completion towards the end of the year. We expect to achieve our goal of 100 participants. The first results are expected to be submitted for publication in 2019.

## Discussion

The outcomes and cost of using an eHealth program to support a patient’s recovery from a THA will be compared with standard care in this RCT. If the eHealth program is found to be effective, implementation into clinical practice could lead to further improvements in patient outcomes. Additionally, the findings of the study will support further research in the use of the eHealth program for other orthopedic surgical procedures such as knee replacements. If the intervention is found to be cost-effective to the hospital, it could support resource efficiency.

Patients scheduled for a revision of THA, a bilateral THA, THA following a fractured neck of femur, or those who have had a previous THA are not included in the trial as their outcomes are likely to be different from those receiving a primary elective THA. A potential limitation of the trial is that in addition to patient self-reported outcome measures, more objective measures of function may have benefitted the trial (eg, the 10-meter walk test and 6-minute walk test). These tests are not included in the study due to the difficulty of conducting these tests pre- and postoperatively, particularly with patients living a distance from the hospital.

The findings from this study will contribute to the current body of literature on eHealth programs in orthopedic care and inform other health professionals on the outcomes of using an eHealth program.

## Abbreviations

CONSORT: Consolidated Standards of Reporting Trial
eHealth: electronic health
EQ-5D-5L: EuroQol EQ-5D-5L
HOOS: Hip Dysfunction and Osteoarthritis Outcome Score
RAPT: risk assessment and prediction tool
RCT: randomized controlled trial
SEMCD: Self-Efficacy for Managing Chronic Disease
THA: total hip arthroplasty
